## Abstract

Type 2 diabetes mellitus (T2DM) is a complex, chronic metabolic disease that carries with it a high prevalence of comorbid conditions, making T2DM one of the leading causes of death in the U.S. Traditional lifestyle interventions (e.g., diet, exercise) can counter some adverse effects of T2DM, however, participation in these activities is low with reasons ranging from physical discomfort to lack of time. Thus, there is a critical need to develop novel management strategies that effectively reduce cardiometabolic disease risk and address barriers to adherence. High-resistance inspiratory muscle strength training (IMST) is a time-efficient and simple breathing exercise that significantly reduces systolic and diastolic BP and improves vascular endothelial function in adults with above-normal blood pressure. Herein we describe the study protocol for a randomized clinical trial to determine the effects of a 6-week IMST regimen on glycemic control and insulin sensitivity in adults with T2DM. Our primary outcome measures include fasting plasma glucose, fasting serum insulin, and insulin resistance utilizing homeostatic model assessment for insulin resistance (HOMA-IR). Secondary outcome measures include resting systolic BP and endothelium-dependent dilation. Further, we will collect plasma for exploratory proteomic analyses. This trial seeks to establish the cardiometabolic effects of 6 weeks of high-resistance IMST in patients with T2DM.

## Introduction

Type 2 diabetes mellitus (T2DM) is at epidemic proportions in the United States, affecting 38.4 million people (https://www.cdc.gov/diabetes/php/data-research/index.html). In 2022, the annual economic cost was $412.9 billion, making it the most expensive chronic condition in the U.S (1).. T2DM is a chronic, obesity-associated metabolic disorder characterized by glucose dysregulation, insulin resistance and beta-cell defects (2, 3). Adults with T2DM are likely to develop vascular endothelial dysfunction and vascular inflammation, increasing their risk of cardiovascular disease (CVD) and the occurrence of cardiac events (4). First-line T2DM treatments include lifestyle modifications, such as dietary changes and exercise (5), the benefits of which are well established in T2DM patients (6, 7).

According to the American Diabetes Association, individuals with T2DM should exercise at least 150-175 minutes per week, incorporating both aerobic and resistance-based activities (8). Although the benefits of exercise for T2DM are well-established, its prevalence continues to rise, likely due in part to inadequate adherence to recommended physical activity guidelines. Studies show that only 41% of adults with T2DM in the U.S. meet the current aerobic exercise guidelines, and only 12% meet the resistance exercise guidelines (9). In comparison, the general population has participation rates of 52% and 21%, respectively (9). Barriers such as physical discomfort and lack of time contribute to these low adherence rates (10, 11). Other factors affecting adherence include socioeconomic status, education level, health status, and physical fitness (12). Additionally, individuals with T2DM often experience reduced exercise tolerance due to early diabetes-related cardiopulmonary impairments, such as reductions in peak workload, peak oxygen uptake, and ventilatory efficiency, which can hinder the effectiveness of exercise training (13). Consequently, many individuals with T2DM remain sedentary, increasing their risk of developing other conditions and comorbidities (14, 15). Addressing and overcoming obstacles to exercise is essential because doing so can greatly enhance the health of patients with T2DM and other related conditions.

Recently, a novel, time-efficient respiratory exercise called Inspiratory Muscle Strength Training (IMST) was developed (16). IMST is distinct from other traditional forms of exercise due to its abbreviated training format (i.e., 5 minutes daily), and is performed using a hand-held device while seated or standing (16). With just six weeks of training (5 days/week), high resistance-IMST has been shown to lower systolic blood pressure (systolic BP) ~9 mmHg in normotensive and hypertensive adults (17). Furthermore, it has been shown to improve endothelium-dependent dilation (EDD) by 45% in older adults with elevated blood pressure (18). These vascular effects of IMST are believed to reduce the risks of CVD, the number one cause of death in people with T2DM (19). IMST is safe and well tolerated, with adherence rates >90% in diverse populations (18, 20), and thus presents a manageable introductory or adjunctive program for improving cardiometabolic health in T2DM patients who have difficulty maintaining a traditional exercise program. However, the effects of IMST on glycemic control and insulin sensitivity, as well as systolic BP and EDD are unknown in patients with T2DM.

Vascular endothelial function and metabolic function are closely linked (21). The vascular endothelium produces nitric oxide (NO), which is released in response to increased arterial wall shear stress (i.e., increased blood flow) (22). Among its various functions, NO enhances glucose uptake into cells and improves insulin sensitivity (23). T2DM is associated with impairments in endothelial function, including reduced NO production and increased vascular inflammation (24). High resistance-IMST is a potentially effective tool to combat T2DM-associated endothelial dysfunction, as it has been shown to increase NO bioavailability and reduce oxidative stress (18)— key adaptations that could improve metabolic health. The latter is especially significant given the link to metabolic syndrome, which encompasses insulin resistance, impaired glucose metabolism, and hypertension (25), and therefore, heightens the risks for cardiac event or stroke (25).

The potential for IMST to elicit cardiometabolic adaptations in diabetic patients warrants assessment. Accordingly, we outline a plan to interrogate the effects of 6 weeks of high-resistance IMST on glycemia (fasting plasma glucose), insulin sensitivity/resistance (fasting serum insulin and Homeostasis Model Assessment [HOMA-IR; ratio of fasting insulin/glucose]), resting BP, and NO-mediated EDD in T2DM patients. Participants will be randomized into either high-resistance (experimental) or low-resistance (control) groups, and complete IMST at home 5 days/week for 6 weeks, with each session lasting ~5 minutes (26). Participants will perform at either high relative resistance (75% of maximal inspiratory pressure in cmH_2_O, (PI_max_)) or low relative resistance (15% of PI_max_) (26). As this is a blinded study, the 15% will ensure participants feel a resistance, but there are not consistent cardiovascular improvements established in previous studies (17, 27, 28).

We will study T2DM patients before and after 6 weeks of high-resistance IMST to test the hypotheses that (1) fasting plasma glucose will decrease, and insulin sensitivity will improve, (2) resting systolic BP will decrease, and (3) high-resistance IMST will improve EDD resulting in clinically-meaningful improvements (i.e., >1% unit change) (29). We will obtain consent to collect blood DNA for banking and plasma for quantitative proteomics analysis. This will allow us to investigate novel protein expression changes before and after IMST. Omic technologies, such as proteomics, provide powerful tools for identifying biomarkers and developing new treatments (30, 31). Our study aims to use quantitative proteomics analyses to identify potential associations and putative markers related to the effects of IMST, which remain largely unexplored. We anticipate observing changes in protein abundance associated with metabolic and cellular processes following IMST, particularly in relation to outcomes in T2DM. However, it is important to note that this exploratory experiment focused on associations rather than mechanisms.

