#### Insulin sensitivity

Insulin sensitivity will be assessed using the Homeostatic Model Assessment for Insulin Resistance (HOMA-IR), a validated surrogate method for estimating insulin sensitivity (32, 33). The equation for HOMA-IR is:

$$HOMA-IR=\frac{\left(fasting\;serum\;insulin\left(\frac{\mu IU}{mL}\right)\right)x\left(fasting\;plasma\;glucose\left(\frac{mg}{dL}\right)\right)}{405}$$

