### Power analysis and sample size

A minimum of 16 and a maximum of 24 participants will be enrolled and randomized into groups. To our knowledge, the effect of IMST on fasting glucose and/or insulin sensitivity in any population have not previously been reported, nor have effects of IMST on systolic BP and EDD in T2DM been specifically ascertained. Thus, for our power analysis we estimated a modest effect size of 0.40 with alpha set at 0.05 using a repeated measures ANOVA within-between framework. A sample size of 16-24 will have 85-96% power for any outcome with an effect size of ≥ 0.40.

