### Statistical plan

Data will be analyzed with a repeated measures ANOVA test and Sidak *post hoc* testing using SPSS version 28.0. We will examine both group-by-sex and group-by-age interactions, and report effect sizes along with confidence intervals, in addition to p-values. All tests will be two-sided with alpha set at 0.05.

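### The Introduction calls HOMA-IR an insulin/glucose ratio, but the outcome equation is a product; separately, a log-scale, baseline-adjusted analysis of insulin and HOMA-IR would be a cheap gain in efficiency

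*Protocol article*

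**What the plan says.** The Abstract names three primary outcomes: fasting plasma glucose, fasting serum insulin and HOMA-IR. The article describes HOMA-IR in two ways.

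- **Introduction**, where the outcomes are outlined: "HOMA-IR; ratio of fasting insulin/glucose".
- **Insulin sensitivity**, under Primary outcomes, where it is called "a validated surrogate method for estimating insulin sensitivity". After the words "The equation for HOMA-IR is" comes a displayed formula: fasting insulin (µIU/mL) multiplied by fasting glucose (mg/dL), divided by 405.

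On analysis, the Statistical plan says "Data will be analyzed with a repeated measures ANOVA test", followed by Sidak post hoc tests, and adds "All tests will be two-sided with alpha set at 0.05". It names no scale, transformation or baseline covariate for any outcome. The Power analysis section works with a generic standardised effect ("we estimated a modest effect size of 0.40 with alpha set at 0.05 using a repeated measures ANOVA within-between framework") and claims 85-96% power with 16-24 participants for any outcome with an effect at least that large. It gives no SD, distribution or scale.

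**The concern.** **Definition.** A ratio and a product of the same two quantities cannot both be HOMA-IR. The primary hypothesis is that glucose falls and insulin sensitivity improves. With insulin unchanged, a fall in glucose lowers the product, which reads as less insulin resistance, but raises the ratio. Taken literally, the Introduction's wording would score the hoped-for glucose change as a worsening.

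**Analysis.** HOMA-IR is a product by construction, so its logarithm is additive in log insulin and log glucose. If insulin and HOMA-IR are right-skewed and respond in proportion to their starting value, then with 8-12 people per arm a few high values can dominate an untransformed mean and variance. A log-scale analysis adjusted for baseline would then use the same data better. At stake is efficiency for two of the three primary outcomes in a small trial.

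**Working it through.** **1. Direction of the two definitions.** Insulin is held at 15 µIU/mL (assumed). The glucose values lie inside the 126-240 mg/dL entry range of Table 1.

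- Glucose 160 to 140, product: 15 × 160 / 405 = 5.93 and 15 × 140 / 405 = 5.19, a change of -12.5%.
- Glucose 160 to 140, ratio: 15 / 160 = 0.094 and 15 / 140 = 0.107, a change of +14%.
- Glucose 126 to 240: the product rises from 4.67 to 8.89, while the ratio falls from 0.119 to 0.0625.

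The reversal does not depend on the insulin value chosen.

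**2. The plan's own power figure.** For the group-by-time test with 2 groups and 2 times, the noncentrality is λ = f² × N × 2 / (1 − ρ), with 1 and N − 2 degrees of freedom. The inputs are f = 0.40, two-sided alpha 0.05 and ρ = 0.5 (assumed; the article gives no correlation).

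- N = 16: λ = 0.16 × 16 × 2 / 0.5 = 10.24, power 84.5%.
- N = 24: λ = 0.16 × 24 × 2 / 0.5 = 15.36, power 96.3%.

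The stated 85-96% is reproduced. Correcting the HOMA-IR wording changes none of it.

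**3. Does the scale matter if f = 0.40 is taken as given?** These are simulations of log-normal data (40,000 trials per setting, ρ = 0.5), with the test on change from baseline.

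- If f = 0.40 holds on the raw scale, raw-scale power at log-SDs of 0.3, 0.5 and 0.7 is 84.5%, 84.6% and 85.3% (N = 16) and 95.6%, 94.9% and 93.9% (N = 24). The loss is about 0-2 points.
- If f = 0.40 holds on the log scale, raw-scale power (N = 16 / N = 24) is 77% / 92% at log-SD 0.2, 70% / 88% at 0.3, 56% / 76% at 0.5 and 43% / 60% at 0.7.

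**4. A fixed proportional effect.** Assume a 25% fall in the high-resistance arm and none in the control arm, with between-person log-SD 0.2-0.7 and within-person log-SD 0.2-0.3. None of these inputs is in the article.

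The log-scale results can be checked by hand:

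- The effect is ln 0.75 = −0.288.
- For log change, the SD is √2 × 0.2 = 0.283, so the standardised difference is 0.288 / 0.283 = 1.02. With 12 per arm the noncentrality is 1.02 × √6 = 2.49, and power is about 66%.
- For ANCOVA, the residual variance is (total log variance) × (1 − ρ²). At log-SDs 0.2/0.2 this is 0.08 × (1 − 0.25) = 0.06, an SD of 0.245, which is smaller than 0.283. At 0.6/0.2, ρ = 0.36 / 0.40 = 0.90 and the SD is √(0.40 × 0.19) = 0.276, so the covariate adds little.

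Power at N = 24:

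| Between / within log-SD | Untransformed change | Log change | Log ANCOVA |
|---|---|---|---|
| 0.2 / 0.2 | 57% | 67% | 77% |
| 0.3 / 0.2 | 55% | 66% | 72% |
| 0.6 / 0.2 | 46% | 66% | 66% |
| 0.7 / 0.3 | 22% | 35% | 36% |

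Across the whole grid, power is about 22-57% for untransformed change and 36-77% for log ANCOVA. When skewness is mild, the baseline covariate supplies about half of the gain. When skewness is strong, nearly all of it comes from the logarithm. At N = 16 and log-SDs 0.6/0.2, untransformed change has 31% and log change about 47%.

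**5. Type I error.** It is about 5% on the log scale. On the raw scale it is about 4-5%, slightly conservative where skewness is strong.

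**The case against.** **On the definition.** The ratio wording is a parenthesis in the Introduction. The outcome section gives a formula with units and a divisor, and anyone computing the outcome would use that. This stands. A reader might infer that the trial will analyse the wrong quantity; the article does not support that. What remains is a contradiction in the current text about a primary outcome, removable by deleting one phrase.

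**On the scale.** A reader might infer that the plan fixes an ANOVA on raw values. It does not. A repeated measures ANOVA of log HOMA-IR would satisfy the Statistical plan as written, and a transformation is a detail that an article commonly leaves to an analysis plan not shown here. The silence is therefore not an error, and the log analysis can only be a recommendation.

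**On the size.** A reader might also infer that the planned analysis loses much of its power. No SD, skewness, correlation or expected percentage change is given for insulin or HOMA-IR, so the size of any loss comes from the assumed inputs. It ranges from about zero, if the effect of 0.40 is meant on the raw scale, to tens of points, if the effect is proportional and the data strongly skewed. That objection also stands, and is why only conditional figures are given. It does not remove the recommendation: with a proportional effect, log ANCOVA beat the untransformed analysis of change in every setting tried, including the mild ones.

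**Conclusion.** The two descriptions of HOMA-IR contradict each other and give opposite signs when glucose changes. Because the outcome section's equation is plainly the working definition, this is a wording correction and changes no power figure.

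The analysis point holds as a recommendation. If insulin and HOMA-IR are right-skewed with proportional changes, log ANCOVA is at least as efficient as an untransformed ANOVA at 8-12 per arm. The advantage is about 36-77% against 22-57% power at N = 24 under an assumed 25% fall and the log-SDs above. If the effect size of 0.40 is defined on the raw scale, skewness costs the raw analysis only about 0-2 points. Neither analysis inflates type I error, so this is a question of efficiency and not of validity. The article's 85-96% power claim is reproduced for the effect size it assumes, and is not shown to be wrong here.

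**What to change.** 1. In the Introduction, delete the ratio gloss and refer to the equation in the Insulin sensitivity section.
2. In the Statistical plan, add one sentence: fasting insulin and HOMA-IR at follow-up will be analysed on the natural-log scale by ANCOVA with the log baseline value as covariate, and the arm effect reported as a ratio of geometric means with a 95% confidence interval. Fasting glucose can stay on its original scale. If an analysis plan already sets the scale and covariate, a reference to it is enough.

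The cost is two sentences, with no extra participants, visits or measurements. The downside is that effects on insulin and HOMA-IR are then read as percent differences and not in the original units.

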## Materials and methods

### Study design

The Diabetes Inspiratory Training (DIT) study is a randomized, sham-controlled, exploratory clinical trial examining the effects of IMST in 24 adults with T2DM. This is a 6-week intervention study design. An outline of the study is shown in **Figure 1**.

**Figure 1 f1:**
[figure not shown]
Study flow for the DIT study.

Participants will perform 5 sets of 6 breaths per day, 5 days per week, at either high relative resistance (75% of maximal inspiratory pressure in cmH_2_O, (PI_max)_) or low relative resistance (15% of PI_max_) (26).

## Participants and interventions

### Study setting and study population

The DIT Study will be conducted at the Clinical and Translational Sciences (CATS) Research Center at the University of Arizona. Participants will be pre-screened over the phone to determine their eligibility using the inclusion and exclusion criteria (**Table 1**).

**Table 1 T1:** Inclusion and exclusion criteria for DIT study.

Inclusions	Exclusions
18+ years old	Current smoker (tobacco/cannabis)
Diagnosed with type 2 diabetes by physician	Uncontrolled medical condition (e.g., cancer)
Fasting plasma glucose levels ≥126 mg/dl and ≤240 mg/dl	Myocardial infarction or stroke within the previous 12 months
SBP between 120-169 mmHg	Performs regular aerobic exercise (>4 bouts/week)
Stable dose of medication (3 months on same dose)	DBP >100 or <60 mmHg
Weight stable in the prior 3 months (< 3 kg weight change) and willing to remain weight stable throughout the study	SBP <120 or ≥170 mmHg
Absence of unstable clinical disease as determined by medical history	Medications that, in the opinion of the study physician or nurse practitioner, may impact the outcomes of the study (e.g., steroids)
	Cheyne-Stokes Respiration
	History or perforated eardrum
	History of glaucoma or retinopathy
	Pregnant, breastfeeding or trying to become pregnant (self-reported)

SBP, systolic blood pressure; DBP, diastolic blood pressure; mmHg, millimeters of mercury; mg/dl, milligrams per deciliter; kg, kilograms; kg/m^2^, kilograms per meter squared.

### Eligibility criteria

Participants will be eligible for this study if they 1) are 18 years of age or older, 2) have been previously diagnosed with T2DM by a physician, 3) have a systolic BP between 120-169 mmHg, 4) are on a stable dose of medication for at least 3 months, 5) do not have an unstable clinical disease, and 6) do not meet the exclusion criteria (**Table 1**). The participants will be asked to maintain their current diet and to not begin any new diet/weight management strategies until their participation in the study is over. We will encourage the participants to eat a balanced meal the day before their scheduled study visit.

### Interventions

All training will be completed using the POWERbreathe™ K3 trainer (POWERbreathe International Ltd., Warwickshire, U.K.). This is a handheld pressure-threshold device with a computerized threshold sensor. Each participant will be provided with their own device on which they will perform IMST at home, 5 days/week for 6 weeks. They will receive in-person verbal instruction on the training protocol and K3 operation from the Research Technician at the start of the study.

The Research Technician will monitor one training session each week in the CATS facility; the remaining 4 sessions will be completed unsupervised at home. During each visit to the CATS facility, the Research Technician will determine the participant’s PImax and transfer the saved training data from the K3 device to ensure exercises are being completed at home. The PImax will be determined by taking the average of 3 measurements. The Research Technician will then adjust the training resistance as needed to ensure participants are training at the prescribed intensity (i.e., either 15% or 75% of PImax). The participant will then perform a supervised training session. Adherence will be assessed by comparing the quantity and quality of completed training sessions to those prescribed. Monitoring will be conducted using the internal data storage of the POWERbreath™ K3 device. Training session data will be downloaded weekly, prior to supervised sessions, to evaluate participant adherence for the preceding week. Participants also will be required to complete a weekly training log to track any additional exercises outside of the daily IMST training. The safety of the training intervention will be assessed by recording any adverse events reported by the participants. Tolerability will be measured by the rate at which enrolled participants dropped out due to adverse events.

## Outcomes

### Primary outcomes

#### Fasting plasma glucose and fasting serum insulin

Participants will report to the CATS facility at the University of Arizona following a 12-hour fast for both the baseline visit and post-intervention visit. Up to 5 mL of blood will be drawn from the antecubital vein and sent to Sonora Quest for screening laboratory tests, lipid measures, and metabolic panels, including fasting plasma glucose and fasting serum insulin.

#### Insulin sensitivity

Insulin sensitivity will be assessed using the Homeostatic Model Assessment for Insulin Resistance (HOMA-IR), a validated surrogate method for estimating insulin sensitivity (32, 33). The equation for HOMA-IR is:

$$HOMA-IR=\frac{\left(fasting\;serum\;insulin\left(\frac{\mu IU}{mL}\right)\right)x\left(fasting\;plasma\;glucose\left(\frac{mg}{dL}\right)\right)}{405}$$

### Secondary outcomes

#### Resting blood pressure

We will measure resting blood pressure per the American College of Cardiology (ACC) and the American Heart Association (AHA) guidelines (26) with an automated oscillometric sphygmomanometer (SunTech CT40, SunTech Medical). Briefly, participants will be asked to sit quietly with both feet flat on the ground, backs supported, and with their arms resting at heart level (26). Three measures will be performed after a 5-minute quiet rest period with 1 minute of recovery between each measure. The average systolic and diastolic blood pressures will be recorded at pre- and post-intervention.

